### Registration of adherence

The participants will be asked to register exercise sessions in a diary and the physiotherapist will register attendance at the supervised exercise sessions. To fulfill the exercise protocol the participants must attend at least 80% of the planned exercise sessions.

Participants in the control group will be interviewed according their exercise habits between test 1 and 2.

# Statistical analyses

The main outcome measure will be analyzed as the between-group change in ASDAS score using ANVOVA with adjustments for baseline scores.

# Ethical considerations

All procedures will be carried out in accordance with the World Medical Association Declaration of Helsinki. The project will apply for approval by the National Committee for Medical Research Ethics, Southern Norway. The patients will be given oral and written information about the study and asked if they are willing to participate. In our opinion neither the testing nor the intervention causes any risk or disadvantages for the participants. Before the exercise intervention the participants will be examined by a Cardiologist to detect any contra-indication to exercise.

#

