### Assessments

All assessments will be conducted at Diakonhjemmet Hospital. An independent assessor, unaware of the assignment to EG or CG, will examine the participants performed before randomization and after the intervention period.

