##### Secondary outcome measures

**Electrocardiography:** to measure the electrical activity of the heart.

**Blood samples:** Analyzed for both general and endothelial specific markers of inflammation and cardiovascular risk (NTproBNP, OPG, RANKL, VEGF, adhesion molecules, TNF-α, IL-6, IL-18, troponin T, high sensitive C-reactive protein, sedimentation rate, total cholesterol, LDL-cholesterol, HDL-cholesterol, triglycerides, apolipoprotein B, apolipoprotein A1, Lipoprotein A).

**Arterial stiffness and endothelial function:**  Measured using the Sphygmocor and Itamar respectively. In addition, the FMD-method will be used to measure endothelial function. Before examination of arterial stiffness at least four hours should have passed from the last meal, cigarette or cup of coffee. 10 hours should have passed from the last intake of alcohol.

**Blood pressure:** Resting diastolic-, systolic and mean arterial blood pressure will be measured.

**Cardiovascular health status:** The patients will be asked to complete a questionnaire reporting on the presence of CVD, the use of medication, smoking, and family history related to the incidence of CVD.

**Physical fitness:** Cardiorespiratory fitness will be assessed with an indirect maximal walking test on a treadmill for estimation of peak oxygen uptake according to modified Balke protocol. Hand grip strength will be assessed with GRIPPIT. Spinal and hip mobility will be assessed with the Bath Ankylosing Spondylitis Metrology index (BASMI), and chest expansion will be measured as the difference between maximal inspiration and expiration at the level of xipoideus (cm).

**Acute physiological responses to exercise:** Will be assessed with a submaximal exercise test (at a fixed work load) and as a part of the maximal treadmill test. The submaximal constant load test will be an integrated part of the warm-up procedure before the maximal treadmill test. Before and immediately after the submaxmial and the maximal bouts, blood samples will be taken. Additional samples will be taken during the maximal test and 5 min post exercise. The blood samples will be analyzed to determine the concentration of  interleukin 6 and 18, tnf-alpha and lactate. Heart rate will be recorded continually during and after the exercise bouts.

**Body composition:** Weight, height, waist circumference will be measured. Dual Energy X-ray Absortiometry (DEXA) will be used to assess body composition.

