### Exercise intervention

The exercise intervention will be carried out at a fitness center with supervision from a physiotherapist.

A cardiorespiratory and muscle strengthening exercise program following the American College of Sports Medicine (ACSM) recommendations for maintenance and improvement of physical fitness. Cardiorespiratory fitness: two interval sessions (4 x 4 min), one continuous moderate exercise session (40 min) on a treadmill. The muscle strength exercises will consist of: 15-20 repetitions, large muscle groups as thighs, back and abdomen.

Dose: 12 weeks. Three times a week, 60 minutes.

Participants in the control group will be asked to continue their usual physical activity habits and will neither be encouraged nor discouraged from exercising. After the intervention period the control group will be offered an individually adapted exercise program and three exercise sessions with supervision from a physiotherapist.

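### The cardiologist's check has to come before training, but the protocol does not require it before the baseline treadmill tests, which are the first hard exercise

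*Protocol*

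**What the plan says.** Under Ethical considerations the protocol sets the timing and aim of medical clearance: "Before the exercise intervention the participants will be examined by a Cardiologist to detect any contra-indication to exercise". The sentence before it reads: "In our opinion neither the testing nor the intervention causes any risk or disadvantages for the participants".

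Under Assessments, a blinded assessor "will examine the participants performed before randomization and after the intervention period", and the place is fixed: "All assessments will be conducted at Diakonhjemmet Hospital". Under Secondary outcome measures, the assessments include "an indirect maximal walking test on a treadmill for estimation of peak oxygen uptake", and a fixed-load bout comes just before it: "The submaximal constant load test will be an integrated part of the warm-up procedure before the maximal treadmill test".

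The training is described separately: "The exercise intervention will be carried out at a fitness center with supervision from a physiotherapist".

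Electrocardiography is listed among the secondary outcomes, and its stated use is "to measure the electrical activity of the heart". Resting blood pressure and a cardiovascular questionnaire are in the same list. The Exclusion criteria name known cardiovascular disease, severe comorbidity that limits exercise capacity, and inability to attend sessions in Oslo.

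**The concern.** The examination exists to find reasons why a person should not exercise. For that it has to come before the first hard exercise, which in this protocol is the baseline treadmill testing and not the first training session. The deadline is tied to the later event.

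What is at stake is patient safety. The Background names cardiovascular events as the main cause of the raised mortality in ankylosing spondylitis. The Inclusion criteria admit people up to age 70 and require that they have done no structured training in the past year. The sponsor has already judged a cardiologist's check worthwhile before exercise; the question is only whether the rule places it early enough.

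**Working it through.** The point concerns the order of procedures, so the check is a reading of the sections side by side. The protocol gives no figure on this point to reproduce.

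**Step 1: the order of events.** Assessments provides one round of tests before randomization and one after the intervention period. Secondary outcome measures puts the submaximal bout and the maximal treadmill test among those tests. The intervention follows allocation. The fixed sequence is therefore: baseline treadmill tests, randomization, 12 weeks of training or usual habits, repeat tests.

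**Step 2: where the check can fall.** Its only bound is the start of the intervention. Two schedules both comply:
- check, baseline tests, randomization, training;
- baseline tests, check (before or after randomization), training.

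Only the first serves the stated purpose for the baseline tests.

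**Step 3: could the intervention be read to include the testing?** Not naturally. Ethical considerations names testing and intervention as two things in the sentence just before the rule. Assessments are dated relative to the intervention period and held at the hospital, while training is at a fitness center. The sites do not show when the cardiologist sees people, but they do show that the protocol treats the two activities as distinct.

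**Step 4: does another provision close the gap?**
- The ECG, blood pressure and questionnaire are outcome measures. No order relative to the treadmill test and no clearance role is given.
- The Exclusion criteria cover disease already known and severe limiting comorbidity. A check meant to detect contra-indications looks for what is not yet known.

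**Step 5: how many tests the wording leaves open.** Sample size and Time schedule give 40 participants, each with one baseline maximal test: 40 × 1 = 40. If everyone is checked first, 0 of 40 tests precede clearance; if everyone is checked between the baseline tests and training, 40 of 40 do. The range counts compliant schedules and is not an estimate.

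**Step 6: who is examined.** The rule refers to the participants without naming a group. If both groups are meant, all 40 are examined. If only the exercise group is meant, then with equal allocation (an assumption; Randomization states blocks but no ratio) 40 / 2 = 20 controls would have no required check before either of their two treadmill tests.

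**The case against.** The strongest reply is that nothing here is wrong on its face. The sentence permits a check before the baseline tests, and visit order is often settled in an operational schedule. The stated aim covers contra-indications to exercise in general, not to training alone. If both groups are examined, the obvious common occasion is the baseline hospital visit, where the same people have an ECG, a blood pressure reading and a cardiovascular questionnaire. The mortality statement also describes patients with the disease at large, whereas this trial excludes known cardiovascular disease.

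Much of this stands. The investigator may well intend an early check, and the trial's participants are at lower risk than the unselected patient population insofar as known disease is excluded. What does not follow is that the text requires an early check. A safety rule with a stated deadline should hold under every schedule that complies with it, and this one does not.

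A reader might go further and infer that the check will follow the maximal test, that participants will be harmed, or that contra-indications found after randomization would unbalance the groups. The documents support none of these. They state no such order, give no rate of undetected contra-indications, and offer no basis for a figure on harm or differential loss.

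**Conclusion.** The point holds as a cheap improvement to patient safety. The protocol's one clearance rule allows the cardiologist's examination to fall after the baseline submaximal and maximal treadmill tests, and no other section requires it sooner. It equally allows an earlier check, so this is a deadline set too late for its purpose, not a contradiction.

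Its size is the 0-to-40 range of tests that the wording leaves uncovered. The conclusion rests on reading the intervention as the training program, which is the natural reading but not a defined term. It does not depend on any assumed rate of contra-indications, and it has no bearing on power, bias or the analysis of the primary outcome.

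**What to change.** Replace the clearance sentence under Ethical considerations with wording such as: *Every participant, in both groups, is seen by a cardiologist before the baseline submaximal and maximal treadmill tests, to look for contra-indications to exercise. Anyone found to have one is neither tested nor randomized.* The clinical content of the examination is for the investigator to set.

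The cost is a fixed order at baseline, with the examination first, plus an examination for each replacement needed to reach 40. If the current text already means both groups, the 40 included need no extra examinations. If only the exercise group was meant, about 20 more are needed, for the controls. The new wording also settles which group or groups are examined.
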